### Measurement scale for TCM symptoms

The measurement scale for TCM symptoms recommended by the *Guidelines for Clinical Research of Chinese Medicine (New Drug)* [16] will be used for ease of assessment. Each of the primary symptoms necessary for the diagnosis of the spleen, kidney deficiency, and blood stasis syndrome will be scored 0, 2, 4, or 6, while secondary symptoms will be scored 0, 1, 2, or 3. The scores will be summed to yield a total score for each set of symptoms for each patient. The total primary symptom score cannot exceed 18 and the total score for secondary symptoms cannot exceed 33 for a patient. The two totals will be added together and any change in this score will be calculated for each patient and used to calculate an efficacy indicator (EI) for the evaluation of treatment efficacy:$$ \mathrm{EI}=\left(\mathrm{Total}\ \mathrm{symptom}\ \mathrm{score}\ \mathrm{at}\ \mathrm{baseline}-\mathrm{Total}\ \mathrm{symptom}\ \mathrm{score}\ \mathrm{post}-\mathrm{treatment}\right)/\mathrm{Total}\ \mathrm{symptom}\ \mathrm{score}\ \mathrm{at}\ \mathrm{baseline}\times \kern0.37em 100\% $$

The degree of symptom improvement will be presented in four categories ranging from full recovery (EI ≥ 90%), good recovery (90% > EI ≥ 70%), and modest recovery (70% > EI ≥ 30%) to no recovery (EI < 30%).

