### Diagnostic criteria for TCM syndrome differentiation

According to the *Guidelines for Clinical Research of Chinese Medicine (New Drug)* [16], a patient has to present with at least two of the primary symptoms and more than two of the secondary symptoms listed below to be diagnosed with the spleen, kidney deficiency and blood stasis syndrome.

Primary signs and symptoms:abdominal masssoreness and weakness of the waist and kneespain or tingling in the backfatiguecold or numbness of limbs

Secondary symptoms:mental listlessnesslower limb edemasubcutaneous petechiasquamous and dry skinchest tightnessfrequent night urinationdark purple or dull red tongue with white furweak, sunken, or strong astringent pulse

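### The stated maximum TCM symptom scores (18 primary, 33 secondary) contradict the protocol's own item list and scoring, which give 30 and 24

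*Protocol article*

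**What the plan says.** The protocol article's section on the measurement scale for TCM symptoms says that primary symptoms "will be scored 0, 2, 4, or 6" and that "secondary symptoms will be scored 0, 1, 2, or 3". It refers to the primary symptoms on which the diagnosis of the syndrome rests. On aggregation it says: "The scores will be summed to yield a total score for each set of symptoms for each patient". It then gives the limits: "The total primary symptom score cannot exceed 18 and the total score for secondary symptoms cannot exceed 33 for a patient".

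The two totals are added. The efficacy indicator (EI) is the fall from baseline divided by the baseline total, as a percentage. It is cut at 90%, 70% and 30% into full, good, modest and no recovery.

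The items themselves appear in the section on diagnostic criteria for TCM syndrome differentiation, which is the only place where symptoms are classified as primary or secondary. It names five primary items (abdominal mass, waist and knee weakness, back pain, fatigue, cold or numb limbs). It names eight secondary items (listlessness, edema, petechia, dry skin, chest tightness, night urination, tongue, pulse).

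The Outcomes section makes change in TCM symptoms a secondary outcome. Table 2 schedules the assessment at all nine visits.

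**The concern.** The item list, the points per item and the summing rule together fix the range of each total. The stated limits do not agree with that range, and they miss in opposite directions: the primary limit is too low, and the secondary limit is higher than any patient could score.

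A site cannot both score all five primary symptoms as described and keep every total at or below 18. Three primary symptoms at the top grade already reach 18, so a fourth has nowhere to go. The scale is used at three hospitals and nine visits, so the conflict leaves room for different handling. The mismatch may also mean that the form in use has a different item set, in which case primary and secondary symptoms carry different weight in the total from what a reader of the article would assume.

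**Working it through.** **Inputs**
- Listed items (diagnostic criteria section): 5 primary, 8 secondary.
- Maximum points per item (measurement scale section): 6 primary, 3 secondary.
- Aggregation (same section): sum within each set, then add the two totals.
- Stated limits (same section): 18 and 33, so 18 + 33 = 51 in total.

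**Step 1. Attempt to reproduce the stated limits.** Maximum = number of items × maximum points per item.
- Primary: 5 × 6 = 30 (stated 18; 12 too low).
- Secondary: 8 × 3 = 24 (stated 33; 9 too high).
- Total: 30 + 24 = 54 (stated 51).

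The stated limits are not reproduced.

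**Step 2. Other readings tried.**
- Item weights swapped: 5 × 3 = 15 and 8 × 6 = 48.
- Only the minimum number of symptoms needed for diagnosis (two primary, three secondary): 2 × 6 = 12 and 3 × 3 = 9.
- Tongue item split into two and pulse item into three: 11 secondary items, 11 × 3 = 33, but primary stays at 30.

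None gives both 18 and 33. Working backwards, 18 / 6 = 3 and 33 / 3 = 11, so the limits imply 3 primary and 11 secondary items, 14 in all against the 13 listed. The Background section describes the same symptoms with the two pulse signs named separately, which makes 14. A 3 + 11 form is therefore conceivable, but the article does not state one.

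**Step 3. Effect on the EI.** EI = (baseline − post) / baseline × 100%. The maxima do not enter.

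(a) *The 13 listed items are summed.* There is no effect.

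(b) *18 is enforced as a limit on the primary total.* Hypothetical patients, primary + secondary:

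| Baseline | Post | EI, no limit | EI, limit 18 |
|---|---|---|---|
| 30+12 | 18+9 | 15/42 = 35.7%, modest | 3/30 = 10%, none |
| 24+8 | 18+4 | 10/32 = 31.25%, modest | 4/26 = 15.4%, none |
| 24+6 | 6+3 | 21/30 = 70%, good | 15/24 = 62.5%, modest |
| 26+8 | 10+4 | 20/34 = 58.8%, modest | 12/26 = 46.2%, modest |

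The last row shows that the category need not change. Of the 4^5 = 1024 possible primary score patterns, 222 (21.7%) exceed 18. This counts patterns, not patients. The secondary limit of 33 can never bind when the listed items reach only 24.

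(c) *A 3 + 11 form is used.* Suppose two of the listed primary items are scored 0 to 3 instead of 0 to 6 and go from severe to mild. The other three primary items stay mild (6 points) and all other secondary points stay at 6.
- As listed: baseline 12 + 6 + 6 = 24, post 4 + 6 + 6 = 16, EI = 8/24 = 33.3%, modest.
- On the other form: baseline 6 + 6 + 6 = 18, post 2 + 6 + 6 = 14, EI = 4/18 = 22.2%, none.

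The primary set's share of the maximum total falls from 30/54 = 56% to 18/51 = 35%.

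**The case against.** The arithmetic is hard to dispute; the consequence is open to challenge. The limits read naturally as a description of the scale's range, much as the pain scale is described by its end points. The article describes no truncation and no range check. The EI does not use the maxima, so if the listed items are summed, every EI and every category is right and the sentence is a descriptive slip.

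It is also fair to say that 18 and 33 are exact multiples of 6 and 3. A coherent 3 + 11 instrument may lie behind them, taken from the cited guideline or set out in the full protocol, neither of which is shown. If one such form is used identically at every visit, the EI is valid for that form and only the article's description is at fault. Finally, the 30+12 example assumes all five primary symptoms at top severity and a post-treatment primary total exactly at the limit. The article gives no score distribution, so the number of patients above 18 is unknown.

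All of this stands as a bound on the consequence. A reader might infer that the most symptomatic patients are truncated at baseline and their improvement hidden. The document does not support that, because it contains no such rule. The inconsistency remains: the scored symptoms are tied to the diagnosis of the syndrome, only one classified list is given, and the limits are stated figures that conflict with it, not details left to another document.

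**Conclusion.** The stated maxima are inconsistent with the scoring applied to the listed items: 18 against 30, 33 against 24, and 51 against 54 in total. This rests only on counting the items and on the stated points.

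The effect on results is conditional. It is nil if the 13 listed items are summed without truncation. Response categories can change if 18 is enforced or if a 3 + 11 form is in use; the article does not say whether either applies. It would go too far to conclude that the efficacy indicator is wrong as planned. The patients in the tables above are illustrations and say nothing about how often a category would change.

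The outcome is one of five named secondary outcomes. The eGFR primary outcome and the sample size, which is based on eGFR, do not depend on it. This should be fixed, but it does not threaten the main result.

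**What to change.** Reconcile the measurement scale section with the diagnostic criteria section:

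- State exactly which items are scored for the outcome, and give maxima that match them: 30, 24 and 54 if the listed items are used.
- State that item scores are summed and totals are not truncated.
- Set any database range checks to the same maxima.
- Score all visits and all three sites in the same way.

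If the outcome form differs from the diagnostic list, set out its items separately in the measurement scale section. Leave the diagnostic list unchanged: it defines eligibility, and the Trial status section says screening ran from October 2018 to July 2019, so editing it would alter the entry criterion after patients had been screened.

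The cost is a sentence or two of text and a look at the data-entry limits. If the items were scored as listed and nothing was truncated, no data change. The formal analysis plan is to be written before database lock, so it can carry the same wording.

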### Pain evaluation scale

Pain is the most common complaint of patients with ADPKD. Causes of pain are multiple but include cyst enlargement, cyst rupture, and secondary infection [22]. Good remission of ADPKD-related pain (low back pain, abdominal pain, headache, chest pain, and leg pain) can alter a patient’s quality of life. The visual analog scale (VAS) is a 10-cm horizontal line anchored by two extremes. It will be used to measure ADPKD-related pain [23]. Patients will be instructed to complete a pain diary for the day at each visit. According to this scale, 0 cm means no pain or no discomfort, whereas the 10-cm end indicates the worst pain or extreme discomfort. The baseline will be the VAS score at visit 2. The difference in pre- and post-treatment VAS scores will be a secondary outcome. At the final visit, patients will complete a global assessment of their overall responses after the trial. The global assessment [24] is a five-point scale: 0 = worsened, 1 = no change, 2 = slightly improved, 3 = improved, and 4 = significantly improved.

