### Measurement items and time points of data collection

Relevant examinations will be performed to collect patient data at 24 weeks before baseline, at baseline, every 4 weeks from 4 to 24 weeks during treatment, and an additional follow-up evaluation will be performed at visit 9 (48 weeks). General information collected will include name, age, gender, ID number, date of birth, home address, contact information, history of present illness, past medical history, family history, personal life history, menstrual history, marital history, allergy history, social history, physical examination results, and laboratory examination results.

There is evidence that age-related TKV can reflect the progress of ADPKD. An MRI scan can accurately measure renal blood flow and evaluate renal cyst compression, which is associated with pain, hypertension, hematuria, albuminuria, and loss of renal function. TKV combined with age and renal function can be used to evaluate the risk of progress to ESRD [19]. The T2 shortening imaging technique of MRI with no radiation damage, no use of gadolinium as a contrast agent, and no risk of nephrogenic systemic fibrosis is recommended and will be used in this study [20]. The outcome is the percentage semi-annual change in TKV measured by MRI, which will be performed at visit 1, visit 2 (24 weeks after visit 1), and visit 8 (24 weeks after visit 2) to observe the growth in kidney volume before and after the intervention.

Items to be measured and the time points of data collection are listed in Table 2.

**Table 2 Tab2:** SPIRIT table: Measurement items and time points of data capture

Items	Screening	Baseline	Treatment						Follow-up
	Visit 1	Visit 2	Visit 3	Visit 4	Visit 5	Visit 6	Visit 7	Visit 8	Visit 9
	−24 weeks	0 weeks	4 weeks	8 weeks	12 weeks	16 weeks	20 weeks	24 weeks	48 weeks
General									
Informed consent	×								
Inclusion and exclusion criteria	×								
Collect general information	×								
General physical examination	×								
Urine hCG (only women)	×								
Medical and drug use history	×								
Concomitant disease and treatment	×								
Combined medication	×	×	×	×	×	×	×	×	×
Effectiveness observation									
Vital signs	×	×	×	×	×	×	×	×	×
TCM symptoms	×	×	×	×	×	×	×	×	×
Pain evaluation	×	×	×	×	×	×	×	×	×
Renal function (eGFR, Scr, BUN)	×	×	×	×	×	×	×	×	×
MRI (TKV)	×	×						×	
Blood electrolytes	×	×			×			×	×
Urine β2-MG, mALB/Cr, RBP	×	×						×	×
Safety observation									
Blood test ^#^	×	×			×			×	×

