### Statistical analysis

A formal and detailed statistical analysis plan will be formulated before the database is locked. The baseline characteristics of both groups, such as gender, age, and smoking status, will be compared by either a χ^2^ test or Student’s *t*-test. Continuous variables will be presented as means ± standard deviations or medians, and differences in such variables will be analyzed using an independent *t*-test or the Wilcoxon signed-rank test. A repeated measurement of variance analysis model of these outcomes will be built.

The difference in eGFR will be tested using two-way ANOVA with repeated measures. Categorical variables will be expressed as numbers and percentages, and differences in such variables will be calculated and compared using a χ^2^ test and Fisher’s exact test. All statistical tests will be two-sided, and the level of significance will be set to *P* < 0.05. Multiple imputation will be used to handle missing data. All patients enrolled will be included in the primary analysis in accordance with the intention-to-treat principle. The statistical analysis will be performed in a blind manner by an independent statistician using SPSS (version 24.0, IBM, NY, USA). No additional analyses or an interim analysis are scheduled.

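### The pain outcome is an unadjusted pre/post difference in visit-day VAS with one baseline reading and no named end visit; a baseline-adjusted mean of readings already collected would be more precise

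*Protocol article*

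**What the plan says.** The Pain evaluation scale section fixes three things.

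- **Recall period:** "Patients will be instructed to complete a pain diary for the day at each visit". Each score describes one day.
- **Baseline:** "The baseline will be the VAS score at visit 2". This is one reading, at week 0.
- **Outcome:** "The difference in pre- and post-treatment VAS scores will be a secondary outcome". The post-treatment visit is not named. Visit 8 (week 24, end of treatment) is the natural reading, but Visit 9 (week 48) also carries a VAS.

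The same section says of the origin of the pain: "Causes of pain are multiple but include cyst enlargement, cyst rupture, and secondary infection".

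Table 2 marks the row "Pain evaluation" at all nine visits: weeks −24, 0, 4, 8, 12, 16, 20, 24 and 48. Six of these are on treatment, in line with the text before the table ("every 4 weeks from 4 to 24 weeks during treatment").

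The Statistical analysis section offers a t-test or a Wilcoxon test for continuous variables and then adds: "A repeated measurement of variance analysis model of these outcomes will be built". It does not name pain, the visits used, or which of these analyses decides the pain comparison. eGFR gets its own repeated-measures sentence.

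**The concern.** Pain reduction is one of the trial's stated hypotheses (Background). Two of the three causes of pain that the protocol names, cyst rupture and secondary infection, can be expected to come and go. A one-day score then varies between days for reasons unrelated to treatment. In a simple difference that variation enters twice, once at baseline and once at the end.

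Pain is also not an entry requirement. Back pain is one of five primary symptoms, of which two are needed, so some patients may score 0 on the baseline day and have no room to improve.

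What is at stake is precision. With about 32 evaluable patients per arm, a wide interval for the pain effect would be hard to interpret. The trial already collects the readings that would narrow it, but the declared outcome does not call for them.

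**Working it through.** **Inputs from the protocol.** 32 evaluable patients per arm (Sample size calculation); two-sided 5% level (Statistical analysis); VAS at Visits 1-9 (Table 2); Visit 2 baseline (Pain evaluation scale). There is no sample size or power figure for pain to reproduce. The 64 evaluable and 72 randomized patients relate to eGFR and are not in question.

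**Assumptions.** The protocol gives no SD or correlation for VAS. I take the variance of one reading as 1 and assume the same correlation r between any two visits, with r = 0.3, 0.5, 0.7.

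**Variance per patient of each possible pain contrast**

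- A. Single post reading minus Visit 2: 2(1 − r)
- B. The same two readings, by ANCOVA: 1 − r²
- C. Mean of the six on-treatment visits minus Visit 2: 1 + (1 + 5r)/6 − 2r
- D. Mean of Visits 6-8, ANCOVA on Visit 2: (1 + 2r)/3 − r²
- E. Mean of Visits 6-8, ANCOVA on the mean of Visits 1 and 2: (1 + 2r)/3 − r²/((1 + r)/2)

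| Contrast | r = 0.3 | r = 0.5 | r = 0.7 |
|---|---|---|---|
| A | 1.400 | 1.000 | 0.600 |
| B | 0.910 | 0.750 | 0.510 |
| C | 0.817 | 0.583 | 0.350 |
| D | 0.443 | 0.417 | 0.310 |
| E | 0.395 | 0.333 | 0.224 |

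Example, D at r = 0.3: (1 + 0.6)/3 − 0.09 = 0.443.

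**Reduction in standard error, 1 − √(variance ratio)**

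| Comparison | r = 0.3 | r = 0.5 | r = 0.7 |
|---|---|---|---|
| B against A (adjustment alone) | 19% | 13% | 8% |
| D against A | 44% | 35% | 28% |
| E against A | 47% | 42% | 39% |
| D against B (averaging alone) | 30% | 25% | 22% |
| E against C | 30% | 24% | 20% |
| D against C | 26% | 15% | 6% |

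Example, D against A at r = 0.3: 1 − √(0.443/1.400) = 1 − 0.563 = 44%.

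**Illustration in power.** Noncentral t, 32 per arm, assumed true effect of 0.5 SD of one reading, for r = 0.3, 0.5, 0.7:

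- A: 38%, 50%, 72%
- C: 59%, 73%, 91%
- D: 84%, 86%, 94%
- E: 88%, 93%, 99%

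**What averaging does not do.** If a pain episode of 3, 7 or 14 days fell at random in the 168 treatment days, one given visit day would lie inside it with probability 3/168, 7/168 or 14/168, about 2%, 4% or 8%. At least one of six visit days would do so with probability about 11%, 25% or 50% (six times as much, since visits are 28 days apart). The episode lengths are assumptions. Even six visit days miss most short episodes.

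**The case against.** The strongest objection is that the intermediate readings may already be used. The repeated-measures sentence directly follows the one on continuous variables, and eGFR is then treated separately, so VAS may well be among the outcomes meant. A change from Visit 2 is compatible with a model that uses every visit. A reader might infer that the plan discards these readings. The documents do not establish that, and for this reason contrast C is shown as an alternative comparator. What stands is that the protocol does not say the model covers VAS or that its result decides.

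Second, change from baseline on a VAS is a conventional endpoint, and a detailed analysis plan is promised before database lock. That is fair for windows and covariates. But the article itself fixes the recall day, the baseline and the form of the outcome, and an analysis plan that follows it literally would inherit contrast A.

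Third, part of the gain is simply ANCOVA against a change score. That is correct: 8-19% comes from adjustment alone, and averaging adds 22-30% on top of contrast B.

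Fourth, late-visit averaging leaves out Visits 3-5 and does not cure missed episodes or a floor at 0. This also stands. The case for the change rests on precision only.

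**Conclusion.** The point holds as a minor precision improvement for a secondary outcome. Against a single-day difference, the standard error falls by about 28-44% with Visit 2 as baseline and 39-47% with the mean of Visits 1 and 2. If the repeated-measures model already averages the six on-treatment visits, the gain is about 20-30% with the Visit 1-2 baseline and 6-26% with Visit 2 alone.

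These figures rest on an assumed equal correlation of 0.3-0.7. Visit 1 lies 24 weeks before baseline and may correlate less, which is why results without it are given. The 0.5 SD effect is illustrative.

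Two stronger readings should be resisted. One is that the outcome cannot capture ADPKD pain because that pain is episodic. The protocol does not call the pain episodic, it lists cyst enlargement first among the causes, and a visit-day score registers persistent pain. Under randomization the contrast is noisy but not biased between arms. The other is that the two readings lie exactly 24 weeks apart, which the text does not say because the post-treatment visit is unnamed. The eGFR sample size is unaffected.

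**What to change.** State in the analysis plan, before unblinding, and align the outcome wording with it:

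1. The pain outcome is the mean VAS over pre-specified late on-treatment visits, for example Visits 6-8 (weeks 16-24).
2. The arms are compared by ANCOVA, or an equivalent baseline-adjusted repeated-measures contrast over those visits, with baseline VAS (Visit 2, or the mean of Visits 1 and 2) and site as covariates. This contrast decides the pain comparison.
3. The Visit 2 to Visit 8 difference is kept as a sensitivity analysis, which also names the post-treatment visit.
4. The general repeated-measures sentence says whether it covers VAS, so that it agrees with the outcome definition.

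The cost is wording only; all readings are already scheduled. The estimate would describe weeks 16-24 rather than week 24, and would be slightly lower if the effect is still growing. Pain between visits remains unmeasured; covering it would need a longer recall period or a diary between visits, which this change does not provide.

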### Statistical analysis

A formal and detailed statistical analysis plan will be formulated before the database is locked. The baseline characteristics of both groups, such as gender, age, and smoking status, will be compared by either a χ^2^ test or Student’s *t*-test. Continuous variables will be presented as means ± standard deviations or medians, and differences in such variables will be analyzed using an independent *t*-test or the Wilcoxon signed-rank test. A repeated measurement of variance analysis model of these outcomes will be built.

The difference in eGFR will be tested using two-way ANOVA with repeated measures. Categorical variables will be expressed as numbers and percentages, and differences in such variables will be calculated and compared using a χ^2^ test and Fisher’s exact test. All statistical tests will be two-sided, and the level of significance will be set to *P* < 0.05. Multiple imputation will be used to handle missing data. All patients enrolled will be included in the primary analysis in accordance with the intention-to-treat principle. The statistical analysis will be performed in a blind manner by an independent statistician using SPSS (version 24.0, IBM, NY, USA). No additional analyses or an interim analysis are scheduled.

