### Randomization

The central randomization list was generated by an independent statistician using SPSS (version 24.0, IBM, NY, USA). Altogether, 36 patients will be assigned to the intervention group and to the control group using a balanced block randomization with 6 blocks. We will randomly select blocks of size 4. Telephone-based randomization will be performed at each coordinating center by an independent physician who is not engaged in recruitment, treatment, or assessment. Participants will be randomly assigned in each site to the YNF group and the placebo group in a ratio of 1:1. After screening, if the patient agrees to participate and voluntarily signs the informed consent form (Additional file 2), the independent physician in each trial site will sequentially assign a random number to them.

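### The rank test named as the alternative to the independent t-test is a paired test, so the non-parametric route for secondary outcomes does not properly compare YNF with placebo

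*Protocol article*

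**What the plan says.** All the relevant text is in the protocol article.

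- **Test for continuous variables (Statistical analysis):** "differences in such variables will be analyzed using an independent *t*-test or the Wilcoxon signed-rank test". The words at issue are "or the Wilcoxon signed-rank test".
- **Summaries that go with it (same section):** "Continuous variables will be presented as means ± standard deviations or medians". No rule says when the median and rank route applies.
- **Further model (same section):** "A repeated measurement of variance analysis model of these outcomes will be built".
- **Primary outcome (same section):** "The difference in eGFR will be tested using two-way ANOVA with repeated measures".
- **Design (Randomization):** "Participants will be randomly assigned in each site to the YNF group and the placebo group in a ratio of 1:1". No matching or crossover is described.
- **Outcomes:** the secondary outcomes are changes in TKV, serum creatinine, BUN, TCM symptoms and pain.

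The article names neither a rank-sum (Mann-Whitney) test nor a paired t-test. It promises a detailed statistical analysis plan before database lock.

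**The concern.** The independent t-test compares two separate groups. Its rank counterpart is the Wilcoxon rank-sum (Mann-Whitney U) test. The signed-rank test is the counterpart of the paired or one-sample t-test. The sentence therefore joins two tests that answer different questions, and the second does not fit a parallel-group trial without matching.

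At stake is what a statistician does who follows the text for a skewed secondary outcome. A bounded 10-cm pain scale, a summed symptom score and a percentage change in kidney volume are plausible candidates for medians. If the named test is run as a one-sample test of change, the result says whether an arm changed, not whether YNF did better than placebo. Under Intervention, both arms receive basic therapy, behavioural intervention and health education, so both could change for reasons unrelated to YNF.

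**Working it through.** **1. The plan's own figure, to fix the scope.** Inputs from Sample size calculation: difference 6, SD 8.53, two-sided α 0.05, power 0.80, ratio 1:1.

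- n per arm = (1.960 + 0.842)² × 8.53² × 2 / 6² = 7.851 × 145.52 / 36 = 31.7, so 32 per arm and 64 in total.
- Dropout of 10%: 64 / 0.90 = 71.1, taken to 72, or 36 per arm.
- Power at 32 per arm: 6 / (8.53 × √(2/32)) = 2.814, and 2.814 − 1.960 = 0.854, which gives 0.803.

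The stated size reproduces and does not depend on the disputed test.

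**2. Ways to run a signed-rank test on these data.** There are two: on change from baseline within one arm, or on differences between patients paired across arms.

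**3. Pairing across arms.** Assumptions, none from the documents: 36 per arm, skewed changes (lognormal, log-scale SD 0.8, centred at median 0), 4,000 simulated trials, arbitrary pairing.

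| Setting | Rank-sum rejects | Signed-rank on arbitrary pairs rejects |
|---|---|---|
| No treatment difference, no common change | 4.3% | 5.0% |
| No treatment difference, both arms shifted 0.5 | 4.9% | 4.9% |
| Treatment shift 0.5 | 78.4% | 58.8% |

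The simulation standard error of the two powers is under one percentage point: √(0.588 × 0.412 / 4000) = 0.008. So this form does not inflate false positives. It loses about 20 points of power (78.4 − 58.8 = 19.6) in this one skewed scenario; the loss should be smaller for data closer to normal. The P value also depends on the arbitrary order in which patients are paired.

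The test cannot be formed at all when arm sizes differ. With all 72 patients kept by multiple imputation, the arms could be equal at 36. On observed cases, with the plan's own 10% dropout allowance, equal arms would be a coincidence.

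**4. Testing within an arm.** This simulation is conditional on a reading that the document does not state, namely that a within-arm P value is taken as evidence about YNF. It assumes normal changes, no treatment difference and the same improvement in both arms.

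| Patients per arm | Common improvement | Signed-rank in YNF arm significant | Rank-sum significant |
|---|---|---|---|
| 32 | 0.35 SD | 46% | 4% |
| 32 | 0.5 SD | 76% | 5% |
| 36 | 0.5 SD | 82% | 5% |

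If p is the within-arm rejection rate, the chance that only the YNF arm is significant is p(1 − p). For 32 per arm and 0.5 SD this is 0.762 × 0.238 = 0.18, which matches the simulated 18%. For 0.35 SD it is 0.456 × 0.544 = 0.25, against a simulated 24%. The figures show only that a within-arm test answers another question. They are not an error rate of the plan.

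**The case against.** The strongest reply is that this is a misnomer. The sentence sets the test beside an independent t-test, so the context is between-group and the rank-sum test was very likely meant. The section also promises a detailed analysis plan before database lock, where the test can be set properly. Both points stand and lower the chance that the wrong test is run. They do not remove the error, because the article names a specific test and that test is wrong for this design.

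Three stronger readings are tempting, and the documents do not support them.

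- **That non-normal outcomes get no valid between-group comparison.** A reader might infer this, but the next sentence promises a repeated-measures ANOVA of these outcomes. That is a randomised comparison, though a parametric one. The routing of pain, TCM score or TKV change to the rank test is also inferred from the mention of medians; no trigger is stated.
- **That the trial will declare YNF effective from within-arm tests.** No within-arm test, paired t-test or conclusion rule of that kind appears in the article. The 76% and 18% figures therefore cannot be charged to the plan.
- **That the ordered recovery categories are mishandled too.** The article says "Categorical variables will be expressed as numbers and percentages" and gives these variables χ² and Fisher tests. For the recovery grades it says "The degree of symptom improvement will be presented in four categories ranging from full recovery", without assigning them a test by name. Either test would be valid. Ignoring order costs power, by an amount that depends wholly on assumed proportions. That is a preference, not an error.

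**Conclusion.** The statement is wrong as written: a paired or one-sample test is named as the alternative to a two-sample test in an unmatched parallel-group trial. The consequence is limited to the non-parametric route for secondary outcomes. Taken literally, that route either misses the treatment comparison or makes it on arbitrary pairs. The latter lowered power from about 78% to 59% in one assumed lognormal setting, with type I error held near 5%. The primary analysis, the sample size and the repeated-measures ANOVA stand. This is a small correction of wording, probably of a slip, and not a threat to the trial's main conclusion.

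**What to change.** In the Statistical analysis section, and in the analysis plan that follows it, replace the signed-rank test with the Wilcoxon rank-sum (Mann-Whitney U) test for between-group comparisons of continuous variables. If a signed-rank test of change within an arm is wanted, name it separately and state that it is descriptive and supports no efficacy conclusion.

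The cost is wording only; 64 evaluable and 72 randomised patients are unchanged. Make and date the correction before database lock and unblinding, because changing a named test later invites questions about selective analysis.
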